### **8.11.1 Statistical Analysis**

For laboratory screening tests of autoimmunity, any change from a normal to an abnormal value or a 2 fold change will be considered a positive result. A patient with any “positive” test will be considered positive and the number of positive tests will not be weighted. A 2 x 2 table will then be constructed to differentiate the frequency of positive patients by treatment group. A  $\chi^2$  test will then be used to assess if these frequencies are statistically significant.

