### **2.2.2      Secondary Objectives**

- To evaluate the safety of daclizumab in the context of vaccinating adult patients with newly-diagnosed high grade gliomas using CDX-110 during recovery from therapeutic TMZ-induced lymphopenia.
- To determine if daclizumab enhances the magnitude or character of CDX-110-induced cellular or humoral immune responses, inhibits or enhances activation-induced cell death, or induces immunologic or clinical evidence of autoimmunity.
- To determine if daclizumab alters the phenotype (CD56-expression), cytokine secretion profile, or cytotoxicity of CD3-CD56+ NK cells.
- To determine if daclizumab in addition to vaccination extends progression free survival compared to historical cohorts.
- To characterize immunologic cell infiltrate in recurrent tumors and seek evidence of antigen escape outgrowth.

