Patients will receive TMZ which will be delivered every 4 weeks. Therefore, in addition to the concurrent TMZ (75 mg/m^2/d) given with radiation, a total of 6 additional cycles of TMZ (100 mg/m^2/days 1-21) will be given. While standard dose 21-day TMZ treatment at a target dose of 100 mg/m^2/day is recommended, TMZ regimen may be adjusted at the discretion of the treating neuro-oncologist. Vaccine will always be given on day  $21 \pm 2$  of each 28 day TMZ cycle. Subsequent vaccines will be given on day  $21 \pm 2$  of each of the five remaining TMZ cycles. Cohort #2 will receive subsequent vaccinations along with daclizumab (1 mg/Kg) on day  $21 \pm 2$  for first 3 cycles. Vaccines will then continue monthly until progression. An additional leukapheresis will be required for any patients who have a positive DTH skin test for PEPvIII for immunologic monitoring.

If the TMZ cycles are completed without progression, monitoring will continue until clinical or radiographic progression without any additional prescribed antitumor therapy. During that time period, patients will be monitored clinically with routine physical and neurologic examinations and MMSE testing at every visit and with a contrasted-enhanced CT or MRI every  $8 \pm 4$  weeks. Peripheral blood will be obtained as outlined in the study flow sheet below for sub-clinical autoimmunity and immunologic monitoring.

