## **8.11 Sub-clinical Autoimmunity**

Patients will also be assessed before vaccine #1 and every 4 months after vaccine # 3 by a panel of clinical laboratory analyses to screen for the development of autoimmunity. The most common manifestations of autoimmunity seen in related trials(Phan, Yang et al. 2003; Attia, Phan et al. 2005; Blansfield, Beck et al. 2005; Jaber, Cowen et al. 2006) have included enterocolitis, dermatitis, uveitis, hepatitis, and hypophysitis. Laboratory evaluations to detect subclinical disease will be obtained as follows: serum thyroglobulin Ab (Lab Code 1802105), rheumatoid factor (Lab Code 5560195), antinuclear Ab (Lab Code 5560214) (Homma, Sagawa et al. 2006); human anti-human (anti idiotypic) Ab ([name] Lab), erythrocyte sedimentation rate (Lab Code 2000860), thyroid-stimulating hormone (Lab Code 1802085), ACTH (Lab Code 1800020), cortisol (Lab Code 1802010), free T4 (Lab Code 1802081), ALT, and AST (Lab Code 1004000). Finally, if

cerebrospinal fluid becomes available, it will be checked for oligoclonal banding (Lab Code 1543440).

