| Immunization #4 (even) (Daclizumab cohort#2)  | Day 21 ± 2 of cycle           |                                                             | X                                                                     | X                 | X                                                                                                           | X                 | X                          |                                          |
| Immunization #5 (odd)                                      | Day 21 ± 2 of cycle           |                                                             | X                                                                     |                   | X                                                                                                           |                   | X                          |                                          |
| EGFRvIII +DTH                                              | +DTH                          |                                                             | X                                                                     |                   | X                                                                                                           |                   | X                          | X                                        |
| Progression                                                |                               |                                                             | X                                                                     | X                 | X                                                                                                           | X                 | X                          |                                          |

 MRI every 8 ± 4 weeks.

 10 Yellow top ACD (9 mL each) and 3 Red top (9 mL each) - all **prior** to vaccine except prior to vaccines #2 and #3 where only 4 Yellow top ACD (9 mL each) and 3 Red top (9 mL each) will be obtained . With vaccine #4, blood work for immunological monitoring will occur monthly before each vaccine. Blood work for autoimmunity monitoring will be obtained prior to vaccine # 1 and every 4 months after vaccine # 3.

 Should be read 48-72 hours after placement

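### The any-positive 2x2 autoimmunity comparison takes no account of how many panels each patient had, so it is biased if follow-up differs between arms

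*Protocol*

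**What the plan says.** Section 8.11.1 fixes three things. At test level, "any change from a normal to an abnormal value or a 2 fold change will be considered a positive result". At patient level, anyone with a positive test "will be considered positive and the number of positive tests will not be weighted". For the comparison, a 2x2 table "will then be constructed to differentiate the frequency of positive patients by treatment group", tested by chi-square. It sets no time window, no denominator of panels drawn and no censoring, so the natural reading is positive at any time on study.

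Section 8.11 schedules the panels "before vaccine #1 and every 4 months after vaccine # 3". A footnote to the flow sheet in section 11 repeats this: "Blood work for autoimmunity monitoring will be obtained prior to vaccine # 1 and every 4 months after vaccine # 3". Neither gives a last panel or a maximum number.

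On length of follow-up, section 5.2.1 says "Vaccines will then continue monthly until progression" and ties the autoimmunity blood to monitoring up to progression. Section 10.3 instead has patients followed for all parameters until death. The flow sheet's Progression row carries a mark in the column that combines autoimmunity and immunologic blood.

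**The concern.** An any-positive outcome accumulates with each panel. A patient with five panels has more chances to cross a threshold than a patient with one, even if nothing differs biologically. The number of panels follows time to progression, or survival on the section 10.3 reading. Both are determined after randomisation, so randomisation does not balance them.

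If daclizumab patients were followed longer, the table would show more autoimmunity than the drug causes. If they progressed sooner, they would be tested less and the drug would look safer. Section 2.1 hypothesises that daclizumab does not induce evidence of autoimmunity, section 3.6 asks for particular attention to it, and 8.11.1 is the protocol's between-arm test of this laboratory panel. The percentages in that table are what a reader would take as the signal.

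**Working it through.** The protocol states no expected rate or power for this comparison, so there is no figure to reproduce. The check asks what the written rule gives when the true risk per panel is identical in both arms.

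**Inputs**
- Saline median time to progression: 12.1 months, the vaccine-treated median in section 3.4.3, here counted from vaccine #1 (assumption).
- Panels: vaccine #3 falls about 0.9 months after vaccine #1 (two 2-week intervals), so panels fall at 4.9, 8.9, 12.9, 16.9 and 20.9 months.
- Assumed, not in the protocol: exponential progression, a 24-month cap, a positive rate q = 20% per panel in both arms, independent panels, and between-arm hazard ratios (HR) of 0.5 and 2.

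**Without a panel at progression.** The probability of reaching the panel at time t is S(t) = exp(−ln2 × HR × t / 12.1).

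| Panel (months) | 4.9 | 8.9 | 12.9 | 16.9 | 20.9 |
|---|---|---|---|---|---|
| Saline | 0.755 | 0.601 | 0.478 | 0.380 | 0.302 |
| Daclizumab, HR 0.5 | 0.869 | 0.775 | 0.691 | 0.616 | 0.550 |
| Daclizumab, HR 2 | 0.570 | 0.361 | 0.228 | 0.144 | 0.091 |

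P(ever positive) is the sum over panels k of q(1−q)^(k−1) × S(t_k). The weights are 0.200, 0.160, 0.128, 0.102 and 0.082.
- Saline: 0.151 + 0.096 + 0.061 + 0.039 + 0.025 = 0.37
- HR 0.5: 0.174 + 0.124 + 0.088 + 0.063 + 0.045 = 0.49
- HR 2: 0.114 + 0.058 + 0.029 + 0.015 + 0.007 = 0.22

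Mean panels (row sums) are 2.5 on saline, 3.5 at HR 0.5 and 1.4 at HR 2.

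**With a panel at progression.** Every patient who progresses before 24 months gets one extra panel. With 1 to 6 panels, 1−(1−q)^J is 0.200, 0.360, 0.488, 0.590, 0.672 and 0.738.
- Saline: shares 0.245, 0.155, 0.123, 0.098, 0.331, 0.049 give 0.48
- HR 0.5: shares 0.131, 0.094, 0.084, 0.075, 0.570, 0.047 give 0.56
- HR 2: shares 0.430, 0.210, 0.133, 0.084, 0.117, 0.027 give 0.37

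**Sensitivity**
- HR 1: identical rates in both arms, so no bias.
- Other values of q, HR 0.5, no progression panel: 22% vs 29% (q = 10%) and 56% vs 72% (q = 40%).
- Within-patient correlation of 0.5 (assumed), HR 0.5, progression panel drawn: 32% vs 35%.
- Cap at 12 months, HR 0.5, progression panel drawn: 33% vs 35%.

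**Effect on the test.** Exact enumeration of the uncorrected chi-square test, 10 per arm, nominal 5%, q = 20%, 24-month cap: without a progression panel it rejects in 3.9% of trials at HR 1, 7.2% at HR 0.5 and 8.7% at HR 2. With one, it rejects in 4.2%, 5.6% and 6.5%.

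**The case against.** The bias needs a between-arm difference in follow-up, and the protocol does not predict one. A reader might infer that it does from the secondary objective, "To determine if daclizumab in addition to vaccination extends progression free survival", but that sentence goes on to name historical cohorts as the comparator. Section 2.1 likewise sets vaccination with or without daclizumab against a historical cohort. The hazard ratios above are therefore illustrations. The possibility still stands: section 10.3 plans a Cox comparison between the groups and makes further interest in daclizumab depend on its not shortening progression or survival.

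A reader might also infer that patients who progress before the first 4-monthly panel have no post-baseline test and count as negative. The documents support neither step. The Progression row marks the combined blood column, so a draw there may include the autoimmunity panel, although the footnote lists only the 4-monthly schedule. Section 8.11.1 does not say how an untested patient is classified.

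If follow-up for all parameters until death governs, the figures based on progression do not apply as they stand; the same mechanism would then run on survival. Independent panels are also a generous assumption, because autoantibody results in one patient are likely to be correlated.

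Finally, section 8.1.1 calls everything beyond the primary endpoint exploratory, and the stopping rules in 5.3.2 and 10.2 rest on dose-limiting toxicity, not on this table. That limits severity. It does not make the comparison sound.

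**Conclusion.** The concern holds in conditional form. Section 8.11.1 itself specifies a crude any-positive comparison on top of an open-ended panel schedule, so this is a choice the protocol has made rather than a detail left for later. Where follow-up differs by arm, the comparison mixes risk per panel with the number of panels; where it does not, there is no bias.

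Under the stated assumptions the spurious gap at HR 0.5 is 12 percentage points without a progression panel and 8 with one. At HR 2 it is 15 or 11 points in the other direction. Correlation within patients or a shorter cap reduces it to a few points. With 10 per arm the test's error rate moves only modestly, so the main damage is to the reported percentages. The per-panel rate, the hazard ratios and the cap are all assumed. Severity is minor: the analysis is secondary and exploratory, and no stated decision depends on it.

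**What to change.** In 8.11.1, make the between-arm comparison time to first positive panel, censored at the last panel drawn, by log-rank or a discrete-time model. In the illustration this compares 20% with 20% per panel, whatever the progression times. If a panel is drawn at progression, index time by panel number, because off-schedule draws come earlier in the arm that progresses faster. Keep the 2x2 table as description, with the number of panels per patient by arm beside it. Reconcile 5.2.1, 10.3, and the flow sheet's Progression row and footnote on when autoimmunity panels stop.

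Positivity at the first scheduled panel after vaccine #3 can be added as a sensitivity analysis. It should not lead: it conditions on reaching that panel (in the illustration at HR 0.5 it leaves out 24.5% of saline and 13.1% of daclizumab patients), and it discards late positives although section 9.2.5 names delayed autoimmune disease as a risk. Late positives should stay in the main analysis.

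The cost is protocol or SAP wording and slightly more analysis, with no new samples. The remaining weakness is that censoring at progression may be informative, which should be stated with the result.

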### **8.12 Whole Blood for Quantitative PCR for EGFRvIII**

Before each immunization, 10 ml of whole blood from each patient will be collected for total RNA extraction. The mononuclear cell fraction of 10 ml of EDTA treated blood was separated by gradient density centrifugation with Ficoll. A total of  $5 \times 10^6 - 1 \times 10^7$  viable cells were used for total RNA extraction with QIAamp RNA Blood Mini kits (Qiagen Cat# 52304) according to manufacture’s instruction. RNA was quantified spectrophotometrically at 260 nm and stored at -80 °C. 1st strand cDNA is synthesized from 1-5 ug of each total RNA with SuperScriptase III (Invitrogen Cat# 18080-051) by following the supplied protocol.

EGFRvIII & EGFR are detected with nested PCR by Taq DNA polymerase Kit with Q-solution (Qiagen) and dUTP substituted for dTTP (Silva, Abraul *et al.* 2006). The 1st round external PCR is mixed in a 50 µL reaction [containing 5–8 µl of cDNA, 1X buffer 1X Q-solution, 200 µM of dNTPs (dATP, dGTP, and dCTP), 600 µM of dUTP, 0.5 µM of each primer (forward: 5’-GTA TTG ATC GGG AGA GCC G-3’; reverse: 5’-GTG GAG ATC GCC ACT GAT G-3’, which cross several exons to assure amplifying cDNA only), 2.5 mM of MgCl2, 3U of Taq DNA polymerase and 1 U of N-uracyl glycosylase (UNG)] and amplified on a thermal cycler [5 min at 25 °C for UNG reaction, 2min at 95 °C for UNG inactivation, 40 cycles of 45 sec at 95° C, 45 sec at 60 °C and 90 sec at 72 °C]. 5 µl of the 1st PCR was used in 2nd internal PCR with primers (forward: 5’-GCG ATG CGA CCC TCC GGG-3’; reverse primer 5’-TCC GTT ACA CAC TTT GCG-3’ which spans exons 8 and 9 junction to eliminate genomic DNA amplification) at the condition (1 cycle of 94 °C for 2 min followed by 35 cycles of 45 sec at 95 °C, 1 min at 55 °C and 1 min at 72 °C). 8 µl of cDNA in 1st PCR and 5 µl of 1st PCR in 2nd PCR are used in the higher RNA dilutions in sensitivity assays with patients’ blood, positive control (EGFR or EGFRvIII expressing cell lines) and negative control samples (normal nucleated blood cells).

352 bp of 1st PCR & 219 bp of 2nd PCR are amplified from EGFRvIII cDNA (GenBank NM\_201283). Both 1st & 2nd PCR products from EGFR cDNA are 801 bp bigger than from EGFRvIII cDNA resolved on a 1.5% agarose electrophoresis gel stained with ethidium bromide (7-10 µL of PCR products each).

Quality of cDNA synthesis is verified by detecting a housekeeping gene glyceraldehyde-3-phosphate dehydrogenase (GAPDH) cDNA (GenBank BC029618) with a 171 bp PCR product of cDNA at above PCR condition except adding less amount of cDNA (1-2 µl of cDNA), changing to GAPDH primers (forward: 5’-TCG CCA GCC

GAG CCA CAT CG-3'; reverse: 5'-GAA CAT GTA AAC CAT GTA G-3') and maintaining 35 cycles with 56 °C of annealing temperature.

The detection of EGFR or EGFRvIII are confirmed by sequencing & aligning the products of the 2nd PCR obtained from positive control samples and from randomly selected positive blood samples. The specificity was also confirmed with no detection of RT-nested PCR in cell lines that do not express EGFRvIII or EGFR and normal nucleated blood cells.

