### **6.2.4 During and After Immunizations**

- Clinical evaluations with each vaccine or leukapheresis will include a general physical, neurologic, and ophthalmologic examination, KPS, and MMSE.
- Radiographic evaluations consisting of a contrast enhanced brain CT or MRI scan will be obtained every 8  $\pm$  4 weeks.
- Blood will be obtained for T4/T8 ratio (Lab Code 2500202), ABC (Lab Code 2010200) with manual differential (Lab Code 2000640), serum for PEPvIII-KLH ELISA ([name] Lab), and 10 yellow ACD (9 mL), 3 red (9 mL), and 1 purple (3 mL) tubes for Immunologic Monitoring *prior* to vaccination #1 and with each vaccination after vaccination #3. Blood will also be obtained for

sub-clinical autoimmunity prior to vaccine # 1 and every 4 months after vaccine # 3. Estimated volume of blood for these tests is 120 cc.

- During TMZ cycles, ABC (Lab Code 2010200) with manual differential (Lab Code 2000640) will be monitored at the time of vaccination (day  $21 \pm 2$ ) and before the next TMZ dosing of each 4 week cycle.
- DTH testing will occur with the fourth vaccination (SOP-JHS-HDC-CL-014 “Delayed Type Hypersensitivity Testing Procedure”). Results will be read and recorded on the appropriate form (FORM-JHS-HDC-CL-014C “Delayed Type Hypersensitivity Testing Form”)  $48 \pm 24$  hours later. An additional leukapheresis will be required for any patients who have a positive DTH skin test for PEPvIII for immunologic monitoring.

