#### **8.12.1     Statistical Analysis**

All data will be background subtracted and compared using **two-sided t-tests** as described above.

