### **10.3.1 Identification of Covariates**

Kaplan and Meier survival curves will be constructed and the Cox proportional hazards model will be used to identify continuous or discrete variables associated with TTP or survival from the immunologic measures and measures of the following predictors: serum EGFRvIII qPCR; serum anti-EGFRvIII titers; EGFRvIII-specific, IFN- $\gamma$  producing, CD8+/CD27-/CD28-/CD45RA-effector memory cells, 5-color positive cells, PEPvIII-KLH-specific tetramer-positive cells, and TReg number and function. Given the large number of predictors that will be examined relative to the overall sample size, it is recognized that these analyses will be exploratory. These analyses are conducted to generate hypotheses only and will need to be validated in additional patients or studies. Statistically, joint effects will also be explored, but are unlikely to have sufficient power to identify such interactions. Assuming that half the sample size of 24 patients are positive for a particular measure and that all have died, we will have 80% power for a logrank test conducted with  $\alpha=0.05$  to detect a survival hazard ratio of approximately 5.04 comparing patients with a positive and negative measure.

In addition, logistic regression and Fisher's exact Chi test will be used to explore whether the covariates outlined above predict the binary outcome of whether or not a patient survives longer than predicted according to Curran's (Curran, Scott et al. 1993) or Lamborn's (Lamborn, Chang et al. 2004) models. For example, for a continuous

predictor dichotomized at its median, given our patient sample size of 20, we will have 80% power to detect a difference in the “success” rate between 30% and 97% with  $\alpha=0.05$ .

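### The blood EGFRvIII assay labelled quantitative is read only as detected or not detected, so the planned t-tests do not fit it; its 10 mL EDTA draw also conflicts with the blood schedule

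*Protocol*

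**What the plan says.** Protocol section 8.12 is headed "Whole Blood for Quantitative PCR for EGFRvIII". The method under that heading is a conventional two-round assay: "EGFRvIII & EGFR are detected with nested PCR by Taq DNA polymerase Kit", with 40 cycles in the first round and 35 in the second. Products are then "resolved on a 1.5% agarose electrophoresis gel stained with ethidium bromide", and EGFRvIII is told apart from wild-type EGFR by fragment size. The GAPDH reaction is a control on the sample: "Quality of cDNA synthesis is verified by detecting a housekeeping gene". The closing paragraph of 8.12 describes blood samples as positive and negative controls as showing no detection.

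The analysis in 8.12.1 reads "All data will be background subtracted and compared using" two-sided t-tests. Section 10.3.1 lists "serum EGFRvIII qPCR; serum anti-EGFRvIII titers" among the predictors of time to progression and survival.

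On the specimen, 8.12 states: "Before each immunization, 10 ml of whole blood from each patient will be collected for total RNA extraction". It specifies EDTA blood and reports an input of 5x10^6 to 1x10^7 viable mononuclear cells. Section 6.2.4 schedules "10 yellow ACD (9 mL), 3 red (9 mL), and 1 purple (3 mL) tubes" before vaccine #1 and with each vaccine after #3, with an estimated total of 120 cc.

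**The concern.** Two separate things do not fit together.

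**Read-out and analysis.** A t-test with background subtraction needs a measured quantity for each patient. The assay as written returns a band or no band. Someone carrying out 8.12.1 would have to invent a number, either a densitometry value after 75 cycles (40 + 35), which the protocol does not describe and which would not be expected to track starting template, or a 0/1 code to which background subtraction does not apply. With 0/1 codes and few positives among about 10 patients per arm, the t-test is unreliable; if neither arm varies, its statistic is undefined. The covariate in 10.3.1 inherits the problem and also names the wrong specimen.

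**Specimen and schedule.** The assay's stated blood volume and visits appear neither in the tube list nor in the flow sheet. If a smaller tube is used by default, low input could turn some true positives into negatives, and it would do so most often in the most lymphopenic samples.

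**Working it through.** **1. What the assay can deliver.** A quantitative PCR result would need at least one of the following; the right-hand column gives what 8.12 contains.

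| Needed for a quantity | In 8.12 |
|---|---|
| Real-time signal or cycle threshold | None; end-point gel |
| Standard curve or copy number | None |
| Normalisation to a reference gene | None; GAPDH is a quality check |
| Limiting-dilution titre | Dilutions appear only in sensitivity assays, with no titre endpoint |

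The result for a patient visit is therefore binary. The protocol already treats binary laboratory results suitably elsewhere: Fisher's exact test for delayed-type hypersensitivity (8.7.1) and a 2 x 2 table for autoimmunity (8.11.1).

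**2. The per-assay power statement.** Section 8.1.1 gives 80% power for a difference above 1.325 sigma with 10 per arm at alpha 0.05. Check by the noncentral t, two-sided: df = 2 x 10 - 2 = 18; noncentrality = 1.325 x sqrt(10/2) = 2.963; power = 0.800. The figure reproduces, but it applies to a continuous outcome and does not carry over to this assay.

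**3. Power for a binary result.** Fisher's exact test, two-sided 0.05, 10 per arm, summing binomial probabilities over the rejecting tables:

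| Detection rate, one arm | Rate needed in the other for 80% power |
|---|---|
| 5% | 70% |
| 10% | 78% |
| 20% | 88% |
| 30% | 95% |
| 50% | not attainable; 62% power even against 100% |

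The last row can be checked by hand. Against 10/10, a count of 5/10 gives p = 0.033 and 6/10 gives p = 0.087, so the test rejects at 5 or fewer. P(X <= 5 | n = 10, p = 0.5) = 0.623.

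**4. Tube volumes.** From 6.2.4: 10 x 9 + 3 x 9 + 1 x 3 = 120 mL, exactly the stated 120 cc. A further 10 mL of EDTA blood would make 130 mL.

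**5. Visits.**

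| Source | EDTA or purple tube | Visits |
|---|---|---|
| 8.12 | 10 mL EDTA | Before every immunization |
| 6.2.4 | One 3 mL purple | Before #1, then with each after #3 |
| Footnote 21 | None at any visit | Reduced ACD and red tubes at #2 and #3 |
| Flow sheet, PCR column | Not applicable | Marked at #1, #4 and #5; blank at #2 and #3 |

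**6. Cell input if only 3 mL is available.** Required concentration = cells / volume.

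- From 3 mL: 5x10^6 / 3 = 1.67x10^6 per mL at the lower end; 1x10^7 / 3 = 3.33x10^6 per mL at the upper end.
- From 10 mL: 0.5x10^6 and 1.0x10^6 per mL.

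Section 3.12 reports lymphocytes below 500/uL (0.5x10^6 per mL) in 70% of 10 patients after a first temozolomide cycle. At that count 3 mL holds under 1.5x10^6 lymphocytes. Monocyte counts are not given. Assuming 300 to 500/uL, the total is at most 3,000 uL x (800 to 1,000) = 2.4 to 3.0x10^6 before separation losses, about half the lower figure. Across assumed yields of 0.5, 1.0, 1.5 and 2.0x10^6 per mL, 3 mL gives 1.5, 3.0, 4.5 and 6.0x10^6 cells, so the lower figure is missed at the first three and met at the last.

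**The case against.** The other side has several good points.

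- **The predictor is not lost.** A reader might infer that the 10.3.1 covariate cannot be derived at all. The section does not support that: it admits discrete as well as continuous variables and frames its power as positive against negative patients. Detected or not detected fits; only a level is unavailable.
- **There is a fallback.** Section 8.2.1 says that here and in other analyses a Wilcoxon rank sum test replaces the t-test when its assumptions fail. On 0/1 data that is a valid comparison of proportions, which limits the harm. It does not supply a quantity from which to subtract background, nor correct the label.
- **Failure of the 3 mL tube is not proved.** It is tempting to say that the tube cannot meet the stated input. No section assigns it to the PCR, and that purple means EDTA is inferred. The cell range describes what was used and is not an acceptance limit. Template is set by RNA mass (1 to 5 ug into cDNA). The lymphopenia figure comes from a 5-day regimen, whereas 5.1.1 targets a 21-day one. What stands is a contradiction in volume and visits: if the purple tube is not for the PCR, no listed tube is identified as EDTA.
- **A temozolomide artefact between arms is not shown.** One might infer that an apparent fall in circulating EGFRvIII would reflect low cell yield. The planned comparisons are between randomised arms on the same temozolomide plan, so an effect on yield should not systematically favour one.
- **The stakes are modest.** Blood EGFRvIII PCR is in no stated objective, and 8.1.1 calls the non-primary analyses exploratory.

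**Conclusion.** The point holds in this form. The documented assay gives a binary result, so 8.12.1 as written does not fit its data, and 10.3.1 misnames both the read-out and the specimen. This rests on the text alone and needs no outside figure. The volume and visit conflict among 8.12, 6.2.4, footnote 21 and the flow sheet is also plain from the text and from the tube sum of 120 mL.

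The cell-yield consequence is conditional. If only 3 mL is used, at least 1.67x10^6 mononuclear cells per mL are needed. That is unlikely under Grade 3 lymphopenia, given the assumed monocyte counts, but not impossible at every visit.

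The correction is worth making because it is cheap. It changes no primary, safety or go/no-go conclusion.

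**What to change.** **Analysis, one of two routes.**

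1. Rename the endpoint as EGFRvIII RT-nested PCR, detected or not detected. Treat GAPDH-negative samples as missing, not negative. In 8.12.1 replace background subtraction and t-tests with Fisher's exact test between the randomised arms. In 10.3.1 enter a binary blood covariate in place of the serum qPCR level. State that only very large contrasts are detectable at 10 per arm (for example, about 10% versus 78% for 80% power). Cost: wording only.
2. If a level is wanted, specify a real-time read-out with a standard curve and normalisation, and keep the t-test. Cost: a different assay to set up.

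**Specimen.** Make 6.2.4, 8.12, footnote 21 and the flow sheet agree on EDTA volume and visits, and name the tube meant for this assay. One option is to exchange one 9 mL ACD tube for an EDTA tube of about 10 mL at the visits actually drawn. The total then moves from 120 to about 121 mL (120 - 9 + 10), at the cost of one fewer ACD tube for the cellular assays.
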